**Methods:**

This is a randomized, single-blind, parallel-group controlled trial conducted in nursing homes in Huzhou, China. A total of 156 older adults with MCI were randomly assigned to either a 12-week, group-based multicomponent exercise intervention or a control group receiving usual care. The intervention, theoretically grounded in an integrated HAPA-TPB framework, integrates aerobic, resistance, and mind–body training with structured behavioral change strategies designed to enhance motivation, adherence, and sustained engagement, including peer interaction. The primary outcome is cognitive function assessed by the Montreal Cognitive Assessment-Basic (MoCA-B). Secondary outcomes include physical performance, sleep quality, intrinsic capacity, frailty, social support, and intervention feasibility.

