#### Secondary outcome measures

Secondary outcomes include Quality of Life measured by the EuroQol-5D-5L (EQ-5D-5L), Activities of Daily Living (ADL), Pittsburgh Sleep Quality Index (PSQI) [29], intrinsic capacity, frailty, social support, and intervention cost and benefit, which have been validated among Chinese older adults. Intrinsic capacity will be evaluated in accordance with the WHO Integrated Care for Older People (ICOPE) guidelines [30], across the following domains: cognitive capacity assessed by MoCA-B, vitality assessed using Mini Nutritional Assessment–Short Form (MNA-SF), locomotion measured by Short Physical Performance Battery (SPPB), psychological status assessed using Patient Health Questionnaire (PHQ-9) [31], and sensory determined by self-reported vision and hearing questions. Frailty will be assessed using the frailty phenotype (FP) [32, 33], physical activity levels will be evaluated using the International Physical Activity Questionnaire–Short Form (IPAQ-SF), and social support will be assessed by the Lubben Social Network Scale (LSNS) [34].

Secondary outcomes will be assessed at baseline, 6 weeks, 12 weeks, and 24 weeks post-randomization. Secondary endpoints will be defined as the between-group differences in change from baseline at each post-randomization timepoint. Results will be reported as adjusted mean differences or risk differences with corresponding 95% confidence intervals, as appropriate to the outcome type. All secondary analyses will follow the intention-to-treat principle.

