### Sample size estimation

The sample size was calculated using PASS 2021 software (version 21.0.3). A two-sample independent *t*-test based on effect size was used for estimation, with cognitive function as the primary outcome. Previous studies have reported effect sizes of exercise interventions on cognitive improvement ranging from 0.54 to 2.85 [36–39]. To ensure a conservative estimation, an effect size of 0.54 for cognitive improvement was selected. With a two-sided significance level of *α* = 0.05 and statistical power of 85% (1 − *β* = 0.85), a minimum of 126 participants (63 per group) was required. To account for an anticipated 20% attrition rate, the planned recruitment target was set at 160 participants (80 per group). Due to unavoidable circumstances, such as relocation or death during the recruitment period, 156 participants were ultimately enrolled, which remained sufficient to meet the predefined statistical power requirements.

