#### Analysis of the primary outcome and secondary outcomes

The primary outcome (MoCA-B score) will be analyzed using linear mixed-effects models (LMM) within a Difference-in-Differences (DID) framework. All available time points (baseline, week 6, week 12, and week 24) will be included in the primary LMM analysis. Fixed effects will include group, time, and the group-by-time interaction, along with relevant baseline covariates (e.g., age and sex). The DID estimate corresponds to the group-by-time interaction term at week 12, representing the between-group difference in change from baseline to week 12 (the primary endpoint). Short-term (baseline to week 6), long-term (baseline to week 24), and durability effects (week 12 to week 24) will also be explored using the same framework. For secondary outcomes, continuous variables will be analyzed using similar linear mixed-effects models. Binary outcomes will be analyzed using generalized estimating equations (GEE) with a binomial family and logit link. Marginal predicted probabilities will be used to derive risk differences between groups. All analyses will be performed in the intention-to-treat (ITT) population.

Missing outcome data will be handled under the missing-at-random assumption using LMM models, which inherently accommodate incomplete repeated measurements. In addition, a sensitivity analysis will be conducted using multiple imputation with chained equations to assess the robustness of the primary results. Exploratory analyses for all outcomes will also be performed using per-protocol analyses to evaluate efficacy among participants who complete the intervention as specified and provide both baseline and 12-week outcome data. Subgroup analyses will be conducted to explore potential heterogeneity of treatment effects. Two-sided *p*-values of less than 0.05 will be considered to indicate statistical significance.

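### The p < 0.05 significance rule is not limited to the primary endpoint, so it also covers about 18–33 secondary tests spread over three visits

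*Protocol article*

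**What the plan says.** Three parts of the protocol article bear on this.

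- **Significance rule.** The section Analysis of the primary outcome and secondary outcomes describes the mixed models for the primary and continuous secondary outcomes, the GEE models for binary outcomes, and the per-protocol and subgroup analyses. It closes by saying that two-sided p-values below 0.05 "will be considered to indicate statistical significance". No outcome or time point is singled out.
- **Secondary endpoints.** Under Secondary outcome measures: "Secondary endpoints will be defined as the between-group differences in change from baseline at each post-randomization timepoint". The post-randomization visits are weeks 6, 12 and 24. The same section plans to report adjusted mean differences or risk differences with 95% confidence intervals.
- **Primary endpoint.** There is one: the between-group difference in MoCA-B change from baseline to week 12. The sample size was set for this comparison alone.

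The analysis section calls the per-protocol analyses exploratory and says that subgroups and the other MoCA-B contrasts are to be explored. It gives the secondary outcomes no such label.

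**The concern.** Unadjusted secondary analyses beside a single primary endpoint are common and acceptable when they are read as supportive estimates. The difficulty here is that the article attaches a declaration of statistical significance to all of them. Each secondary outcome has three chances to meet the threshold, and none of the three visits is marked as the decisive one.

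Followed as written, the rule would let a chance result on sleep, frailty or quality of life at any one visit be reported as statistically significant. The Discussion says the findings will inform integrated care strategies for cognitive and physical health and may support wider use of exercise programmes in long-term care. A spurious secondary result could therefore carry weight.

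**Working it through.** **1. The plan's own figure.** Inputs, from Sample size estimation: two-sided α = 0.05, "statistical power of 85"%, and "an effect size of 0.54 for cognitive improvement was selected". The two-sample t-test (noncentral t) gives power 84.7% at 62 per group and 85.25% at 63 per group. This reproduces the statement that "a minimum of 126 participants (63 per group) was required". The calculation covers one test at 0.05. It is sound and not in dispute.

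**2. Number of secondary tests.** Each outcome counts three times (weeks 6, 12 and 24).

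| Outcomes counted | Outcomes | Tests |
|---|---|---|
| EQ-5D-5L, ADL, PSQI, intrinsic capacity, frailty, social support | 6 | 18 |
| plus cost and benefit | 7 | 21 |
| plus physical activity (IPAQ-SF) and physical performance (SPPB) | 9 | 27 |
| plus MNA-SF and PHQ-9 | 11 | 33 |

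The additions depend on the reading. Cost and benefit may not be tested as a change score. IPAQ-SF is described in the section but is not in its opening list. SPPB appears there only as a domain of intrinsic capacity, although the abstract names physical performance as a secondary outcome. MNA-SF and PHQ-9 appear only as domains of intrinsic capacity.

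**3. Expected false positives if no secondary outcome is affected.** 0.05 × m, whatever the correlation: 0.05 × 18 = 0.90 and 0.05 × 33 = 1.65.

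**4. Chance of at least one, independent tests.** 1 − 0.95^m: 1 − 0.95^18 = 0.603, 1 − 0.95^21 = 0.659, 1 − 0.95^27 = 0.750, 1 − 0.95^33 = 0.816.

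**5. Chance of at least one, correlated tests.** The protocol gives no correlations, so these values are assumptions. Correlated normal test statistics were simulated and |z| > 1.96 counted as significant. The correlation between two different outcomes at two different visits was taken as the product of the outcome and visit correlations.

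| Outcome correlation | Visit correlation | 18 tests | 21 tests | 27 tests | 33 tests |
|---|---|---|---|---|---|
| 0.3 | 0.5 | 51% | 56% | 64% | 71% |
| 0.3 | 0.7 | 46% | 51% | 59% | 65% |
| 0.5 | 0.5 | 45% | 49% | 56% | 61% |
| 0.5 | 0.7 | 40% | 44% | 50% | 55% |
| 0.5 | 0.9 | 32% | 35% | 41% | 45% |

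A visit correlation of 0.5 is what changes sharing one baseline would have if all visits were equally correlated.

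**The case against.** The strongest reply is that this belongs to the statistical analysis plan, which the article says will be signed before database lock. That plan may rank the secondary outcomes, add a multiplicity rule or call them supportive. The threshold sentence could also be read as merely defining a word. This stands in part: the lack of an adjustment method in a journal article is no fault. What remains is stated text, namely an unrestricted significance rule together with an endpoint at every visit. A plan that limited significance to the primary endpoint would have to depart from the published rule.

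A second reply is that much of the safeguard is already present: estimates with 95% confidence intervals are planned, and the per-protocol, subgroup and other MoCA-B analyses are called exploratory or explored. That is correct. It narrows the point to the secondary outcomes and makes the change small.

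A reader might go further in three ways that the document does not support.

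- That a false significant secondary result is more likely than not. This holds under independence. Under correlation it depends on the count and the values assumed: for 18 tests, outcome correlation 0.3 and visit correlation 0.7 give 46%, and even 33 tests give 45% under very strong correlation.
- That the secondary family is unfixed because the abstract's list differs: "Secondary outcomes include physical performance, sleep quality, intrinsic capacity, frailty, social support, and intervention feasibility". An abstract that condenses a list does not show this, and feasibility corresponds to the process evaluation.
- That the primary conclusion is weakened. It is one outcome, one time point and one contrast.

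**Conclusion.** The point holds as a fault of wording with a real consequence. The article extends one two-sided 0.05 significance rule to secondary outcomes that are each defined as endpoints at three visits. Even the lowest probability computed, about 32%, is more than six times the nominal 5%. The expected number of false positives, about 1 to 1.6, rests only on the test count and on no secondary outcome being affected. The probabilities rest in addition on correlations that the document does not give, and should be quoted as a range. The primary endpoint's error rate, its power and the sample size are not in question.

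**What to change.** Reword the last sentence of Analysis of the primary outcome and secondary outcomes along these lines:

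> Statistical significance, at two-sided p < 0.05, will be judged for the primary endpoint only (MoCA-B change from baseline to week 12). Secondary outcomes are supportive. They will be presented as effect estimates with 95% confidence intervals, without adjustment for multiplicity, and will not be declared significant. The same applies to the per-protocol and subgroup analyses and to the other MoCA-B contrasts.

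The statistical analysis plan should carry the same statement before it is signed. The estimates and intervals are already planned for the secondary outcomes, so no analysis is added and no new data are needed.

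The cost is that the sponsor gives up the word significant for secondary outcomes. If it wants to keep that wording, a multiplicity procedure over a named family is the alternative. Holm's method would start at 0.05/18 = 0.0028 to 0.05/33 = 0.0015. Looking at week 12 alone without adjustment would not be enough: 6–11 independent tests still give 1 − 0.95^6 = 26% to 1 − 0.95^11 = 43%.

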### Trial monitoring

Trial conduct will be monitored by the core research team to ensure adherence to the study protocol, data quality, and participant safety. Monitoring activities will include regular review of recruitment progress, participant adherence, data completeness, and documentation of adverse events. Monitoring will be conducted on a monthly basis through team meetings and periodic review of study records. Any protocol deviations will be documented and discussed within the research team. Serious adverse events will be reported promptly to the institutional ethics committee in accordance with regulatory and institutional requirements. Decisions regarding potential trial modification or termination will be made by the principal investigator in consultation with the ethics committee. Given the low-risk nature of this behavioral exercise intervention, an independent data monitoring committee has not been established, and no formal interim analyses or predefined stopping guidelines are planned.

## Results

### Baseline characteristics of randomized participants

A total of 1351 participants completed preliminary eligibility screening. Based on MoCA-B results, 156 participants met the inclusion criteria and were subsequently randomized into either the intervention group (*n* = 78) or the control group (*n* = 78) and baseline assessments (week 0) were completed **(**Fig. 2**).**

**Fig. 2 Fig2:**
[figure not shown]
Trial profile

Baseline characteristics are presented in Table 3. A total of 156 participants were randomized to either the exercise intervention group (*n* = 78) or the control group (*n* = 78). The mean age of the total sample was 69.19 years (SD = 8.97), with a higher proportion of female participants (*n* = 108, 69.23%) than male participants (*n* = 48, 30.77%). The two groups were generally well-balanced at baseline, with no statistically significant differences observed in age, gender, marital status, educational attainment, Hukou status, occupation and monthly income.

**Table 3 Tab3:** Baseline characteristics of participants

**Variable**	**Intervention group** (*N* = 78)	**Control group** (*N* = 78)	*χ*^2^/*F*	*P* value
**Age (year)**	68.63(8.61)	69.76(9.35)	0.610	0.434
**Sex**			0.120	0.729
Male	23 (29.49)	25 (32.05)		
Female	55 (70.51)	53 (67.95)		
**Marital status**			0.027	0.869
Married or partnered	48 (61.54)	49 (62.82)		
Other	30 (38.46)	29 (37.18)		
**Educational attainment**			0.026	0.872
Primary school and below	42 (53.85)	43 (55.13)		
High school and above	36 (46.15)	35 (44.87)		
**Hukou**			0.103	0.748
Urban	37 (47.44)	35 (44.87)		
Rural	41 (52.56)	43 (55.13)		
**Occupation**			2.136	0.711
Government or institutional staff	7 (8.97)	4 (5.13)		
Skilled professional/technical personnel	6 (7.69)	6 (7.69)		
Agricultural workers	10 (12.82)	14 (17.95)		
Others	47 (60.26)	43 (55.13)		
Unemployed or not currently working	8 (10.26)	11 (14.10)		
**Household income per month**			0.045	0.978
Low income (tertile 1)	28 (35.90)	28 (35.90)		
Middle income (tertile 2)	33 (42.31)	34 (43.59)		
High income (tertile 3)	17 (21.79)	16 (20.51)		

Continuous variables are reported as mean ± SD and analyzed using ANOVA; categorical variables are reported as frequency (%) and analyzed using chi-square tests

Table 4 presents the baseline health status of participants. No significant between-group differences were detected across a range of health indicators. The health status was generally comparable between groups. Baseline values for self-rated health, MNA-SF, SPPB, PHQ-9, PSQI, ADL, frailty, social support situation, and MoCA-B were also well-balanced. Although self-rated health scores were slightly higher in the intervention group, the control group reported marginally poorer sleep quality. Cognitive function, assessed by the MoCA-B, was also similar between groups, with mean scores of 17.29 (SD = 2.32) in the intervention group and 16.74 (SD = 2.19) in the control group. Overall, these findings indicate that both randomized groups were comparable at baseline in terms of both demographic characteristics and health status, providing a sound basis for evaluating the intervention effects.

**Table 4 Tab4:** Baseline health status of participants

**Variable**	**Intervention group** (*N* = 78)	**Control group** (*N* = 78)	*χ*^2^/*F*	*P* value
**Self-rated health, mean (SD)**	71.76 (9.00)	69.50 (8.33)	2.670	0.104
**Nutritional status (MNA-SF)**			1.378	0.502
Normal nutritional status	24 (30.77)	26 (33.33)		
At risk of malnutrition	47 (60.26)	41 (52.56)		
Malnourished	7 (8.97)	11 (14.10)		
**SPPB, mean (SD)**	7.30 (2.75)	6.96 (2.86)	0.540	0.463
**Depression status (PHQ-9)**			0.289	0.591
No	58 (74.36)	55 (70.51)		
Yes	20 (25.64)	23 (29.49)		
**PSQI, mean (SD)**	11.95 (4.62)	13.46 (7.45)	2.320	0.130
**Distance vision**			2.937	0.087
Good	6 (7.69)	13 (16.67)		
Poor	72 (92.31)	65 (83.33)		
**Near vision**			6.798	0.009
Good	2 (2.56)	11 (14.10)		
Poor	76 (97.44)	67 (85.90)		
**Hearing**			0.880	0.348
Good	7 (8.97)	4 (5.13)		
Poor	71 (91.03)	74 (94.87)		
**ADL score, mean (SD)**	21.32 (7.08)	22.31 (7.58)	0.710	0.402
**Frailty status (FP)**			1.354	0.245
No	61 (78.21)	65 (83.33)		
Yes	17 (21.79)	13 (16.67)		
**Limited social network**			0.104	0.747
No	35 (44.87)	33 (42.31)		
Yes	43 (55.13)	45 (57.69)		
**Cognitive status**				
**MoCA-B score, mean (SD)**	17.29 (2.32)	16.74(2.19)	2.320	0.130

*MNA-SF *Mini Nutritional Assessment–Short Form, *SPPB *Short Physical Performance Battery, *PHQ-9 *Patient Health Questionnaire-9, *PSQI *Pittsburgh Sleep Quality Index, *MoCA-B *Montreal Cognitive Assessment-Basic (Chinese version). Continuous variables are reported as mean ± SD and analyzed using ANOVA; categorical variables are reported as frequency (%) and analyzed using chi-square tests

## Discussion

This protocol outlines a rigorously designed randomized controlled trial aiming to evaluate the effects of a 12-week, theory-informed multicomponent exercise intervention on cognitive and physical function among older adults with MCI residing in nursing homes in China. Given the growing aging population and increasing prevalence of MCI in institutionalized settings, there is an urgent need for effective, scalable interventions that address both physical and cognitive health. This MIND-STEP study seeks to address a key evidence gap by implementing a structured program grounded in the integrated HAPA-TPB, combining aerobic, resistance, and mind–body exercises with behavioral strategies to promote adherence and long-term engagement.

The baseline characteristics of the study cohort demonstrated that participants were representative of the broader population of older adults with MCI in residential care, with a mean age of 69.19 years and a predominance of female participants, consistent with demographic trends in nursing homes. Importantly, no significant between-group differences were observed across demographic, socioeconomic, or health-related variables, suggesting that the randomization process was successful and that the two arms are comparable at baseline. This provides a robust foundation for assessing intervention effects on subsequent outcomes. A key strength of this trial lies in its integration of behavioral theory into the intervention framework. By embedding motivational and volitional strategies derived from the HAPA-TPB model, the program is designed not only to enhance short-term participation but also to foster long-term behavior change. The group-based delivery format, coupled with tailored support strategies such as action planning, social reinforcement, and coping strategies, is expected to improve feasibility and acceptability in nursing home settings. Nonetheless, several potential limitations warrant consideration. First, as the trial is conducted in nursing homes within a single urban region, generalisability to community-dwelling older adults or those in rural areas may be limited. Second, while the follow-up period captures short- to mid-term effects, longer-term sustainability of intervention benefits remains to be evaluated. Third, although efforts have been made to blind outcome assessors and standardize procedures, some risk of performance or detection bias cannot be fully excluded. Finally, repeated administration of the MoCA-B may introduce practice effects, which could partially inflate cognitive scores over time. Although both groups were assessed at identical time points and the primary analysis focused on between-group differences, residual practice effects cannot be fully excluded.

In conclusion, this trial will contribute novel evidence on the effectiveness and implementation of a structured, multicomponent exercise intervention for older adults with MCI, supported by behavioral theory and delivered in a nursing home setting. The findings will inform the development of integrated care strategies targeting cognitive and physical health in aging populations and may support broader adoption of exercise-based interventions within long-term care services in China and beyond.

## Data Availability

Access to de-identified data may be granted to interested parties 12 months after the publication of the principal paper addressing primary research questions, upon request via email to the responsible person ([contact]).
